# Bilateral cervical plexus block for anterior cervical spine surgery: study protocol for a randomised placebo-controlled trial

**DOI:** 10.1186/s13063-021-05377-4

**Published:** 2021-06-29

**Keywords:** Superficial cervical plexus, Cervical spine surgery, Randomised controlled trial, Placebo

## Abstract

**Background:**

There has been increasing focus to improve the quality of recovery following anterior cervical spine surgery (ACSS). Postoperative pain and nausea are the most common reasons for prolonged hospital stay and readmission after ACSS. Superficial cervical plexus block (SCPB) provides site-specific analgesia with minimal side effects, thereby improving the quality of recovery. The aim of our study was to investigate the effect bilateral cervical plexus block has on postoperative recovery in patients undergoing ACSS.

**Methods:**

The study is a pragmatic, multi-centre, blinded, parallel-group, randomised placebo-controlled trial. 136 eligible patients (68 in each group) undergoing ACSS will be included. Patients randomised to the intervention group will have a SCPB administered under ultrasound guidance with a local anaesthetic solution (0.2% ropivacaine, 15mL); patients randomised to the placebo group will be injected in an identical manner with a saline solution. The primary outcome is the 40-item quality of recovery questionnaire score at 24 h after surgery. In addition, comparisons between groups will be made for a 24-h opioid usage and length of hospital stay. Neck pain intensity will be quantified using the numeric rating scale at 1, 3, 6 and at 24 h postoperatively. Incidence of nausea, vomiting, dysphagia or hoarseness in the first 24 h after surgery will also be measured.

**Discussion:**

By conducting a blinded placebo trial, we aim to control for the bias inherently associated with a tangible medical intervention and show the true treatment effect of SCPB in ACSS. A statistically significant result will indicate an overall improved quality of recovery for patients; alternatively, if no benefit is shown, this trial will provide evidence that this intervention is unnecessary.

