## Background

Anterior cervical discectomy and fusion (ACDF) is a common surgical procedure for cervical spine disease. There has been an increasing focus on reducing the length of hospital stay after this procedure. Whilst the mean length of stay has been reported to be approximately 2 days, some centres are performing this procedure in an outpatient setting [1–4]. The approach for anterior cervical disc arthroplasty is the same for ACDF, and there is a trend towards performing this procedure in the outpatient setting too [5]. We will hereafter refer to these two operations under the heading anterior cervical spine surgery (ACSS).

Postoperative pain and nausea are the most common reasons for prolonged hospital stay and readmission after ACSS. [6, 7] Pre-emptive analgesia with regional anaesthesia is a method used to improve postoperative pain management. The superficial cervical plexus block (SCPB) has been used for neck surgeries for this reason [8]. The cervical plexus is formed by the anterior rami of the upper four cervical nerves and lies deep to the prevertebral fascia on the scalenus medius. In a SCPB, local anaesthesia is infiltrated at the punctum nervosum, anaesthetising four superficial branches of the cervical plexus: the lesser occipital, the great auricular, the transverse cervical, and the supraclavicular nerves. The distribution of these nerves includes the anterior and lateral neck, and the pre- and post-auricular areas.

SCPB is a safe technique that has been shown to provide good relief for incisional pain after thyroid and carotid surgeries, and relief of occipitonuchal pain after neurosurgical procedures [8–11]. It may also reduce opioid consumption and therefore the related side effects, such as nausea, vomiting, and respiratory depression. Finally, a goal of the SCPB is to improve the overall quality of recovery from surgery from the patient’s perspective.

The aim of this study is to investigate the effect bilateral cervical plexus block with local anaesthesia has on postoperative recovery in patients undergoing ACSS. The hypothesis is that bilateral SCPB is superior to placebo in patients undergoing ACSS in improving post-operative recovery, as measured by the 40-item quality of recovery (QoR-40) score at 24 h.

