### Primary outcome

The primary outcome will be the QoR-40 score measured at 24 h post-operation completion time. The ‘quality of recovery’ score was developed to provide a patient-orientated assessment of the quality of recovery after surgery and anaesthesia [14]. This was later expanded to the QoR-40 score. This score was validated and shown to be reliable when completed on the first post-operative day [15]. The score measures five dimensions of patient experience: pain, emotional state, physical independence, comfort and psychological support. A systematic review showed that the QoR-40 was a widely used, valid, reliable and responsive tool for assessing quality of recovery from a patient perspective [16].

The minimum clinically important difference (MCID) can be thought of as the smallest change that is important to a patient and is an especially important concept in studies involving patient-reported outcomes [17]. There are various methods of determining MCID. A 2016 study, using the anchor method, determined the MCID to be 6.3 for the QoR-40 score [18]. Based on cardiac studies, one author argued that a change of 5–7 signifies a clinically important difference in the QoR-40 score [19]. A randomised study of patients undergoing cervical spine surgery predefined the MCID as a change of 10 [20]. In a prospective study of patients undergoing neurosurgery procedures, the mean QoR-40 at post-operative day 1 in 92 patients undergoing spinal surgery was 160 (SD-15) [21]. Based on the distribution-based approach of determining MCID (that is, half standard deviation), the MCID would be 7.5. Taking this into account, we chose a change of 7.5 to signify a clinically important change in a spinal surgery setting.

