### Sample size calculation

The primary endpoint is the QoR-40 score at 24 h post-operatively, and thus, we are planning a study of a continuous response variable from independent control and experimental subjects with 1 control per group. We used an MCID of 7.5 for the QoR-40, as discussed above. If the true difference between the groups is 7.5, we will need a study of 64 subjects in each group to be able to reject the null hypothesis that the population means of the experimental and control groups are equal with probability (power) 0.8. The type 1 error associated with this test of the null hypothesis is 0.05.

Allowing for a dropout rate of 5%, we will randomise 136 patients (68 in each group). The software used to do the calculation was PS from the University of Vanderbilt, USA.

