### Statistical analysis

Baseline characteristics will be summarised by treatment group to assess comparability. We are not planning to adjust the analyses for baseline variables.

Data analysis will be performed according to the intention-to-treat principle. The primary outcome will be analysed by a comparison of scores using an independent t test, with 95% confidence intervals and two-tailed p values reported. Significance levels will be set at 0.05.

The 24-h opiate usage and hospital length of stay will by analyses using independent t tests with 95% confidence intervals and two-tailed p values reported.

Nausea and vomiting will be recorded as categorical variables and analysed using the Pearson chi-squared test.

For the analysis of pain scores across the four periods a linear regression analysis will be used with the dependent variable being the pain score and the independent variables being ‘period’, ‘group’ and ‘period*group’ interaction. This analysis will be conducted within the framework of Generalised Estimating Equations, which corrects the bias in the estimates of the SE caused by having multiple observations per person and thus correlation in the data. The output generated would be the difference between the groups across all periods (95% CI and p value) and the difference between the groups in each period (95% CI and p value).

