Placebo-controlled trials are particularly important when outcomes are based on patients’ subjective rating [26]. This trial is justified because there is a need to [1] demonstrate the true treatment effect of this intervention, [2] control for the bias that is associated with the tangible intervention and [3] provide a quantification of the adverse events of this intervention.

The anticipated benefits of SCPB in ACSS include improved post-operative pain control, resulting in a reduced length of hospital stay, decreased opioid requirements and an improved patient experience. Alternatively, this placebo-controlled trial may demonstrate no benefit from SCPB, and in that case, an unnecessary percutaneous procedure and administration of a medication will be avoided.

Potential limitations of this trial include a possible slow rate of recruitment secondary to patient concern over participating in an interventional placebo trial. This is a well-known issue for placebo trials (in surgery in particular); however, these trials are important and have been shown to be feasible [27, 28]. Second, we have chosen a power of 80% in our sample size calculation. Whilst this could be regarded as low power, it is consistent with conventional values; although we do acknowledge the possibility of type II error if the effect size is not as strong as predicted [29].

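### The article would read a failure to show superiority as evidence that the block is unnecessary, without requiring the confidence interval to exclude the 7.5-point important difference

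*Protocol article*

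**What the plan says.** The abstract's Discussion paragraph pairs two outcomes. On one side, "A statistically significant result will indicate an overall improved quality of recovery for patients". On the other, "if no benefit is shown, this trial will provide evidence that this intervention is unnecessary". The main Discussion returns to the second: "this placebo-controlled trial may demonstrate no benefit from SCPB, and in that case, an unnecessary percutaneous procedure and administration of a medication will be avoided".

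The design behind these sentences is superiority only. The Background states that "The hypothesis is that bilateral SCPB is superior to placebo in patients undergoing ACSS". Under Sample size calculation, "The type 1 error associated with this test of the null hypothesis is 0.05", with 64 per arm for 80% power at a true difference of 7.5. Under Statistical analysis, the primary outcome is compared "using an independent t test, with 95% confidence intervals and two-tailed p values reported".

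The Primary outcome section sets the MCID at 7.5, half of an SD of 15. It also cites other values: "A 2016 study, using the anchor method, determined the MCID to be 6.3 for the QoR-40 score", an argued range of 5 to 7 from cardiac studies, and 10 as predefined in a randomised cervical spine surgery study. No section says how the confidence interval should be set against any of these values before the block is called unnecessary.

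**The concern.** In the abstract, the counterpart of a significant result is a result in which no benefit is shown. Read naturally, that means a non-significant superiority test. Failing to reject equality of means does not show that a worthwhile difference is absent. It shows that only if the interval is narrow enough, and placed low enough, to exclude the difference that matters.

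At stake is the trial's practical message. The main Discussion says that after a negative finding the procedure would be avoided. If that finding came from an interval still containing 7.5, the trial would be cited against the block while its own data remained compatible with an effect the protocol calls clinically important.

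**Working it through.** **Inputs.** SD 15, MCID 7.5 and the cited values 6.3 and 5 to 7 (Primary outcome); 64 per arm, power 0.80, alpha 0.05, 5% dropout, 68 per arm randomised (Sample size calculation); two-tailed t test with 95% interval (Statistical analysis). The sample size section does not restate the SD. That 15 was used is an inference, and step 1 supports it. Differences are block minus placebo, with higher scores better.

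**1. The plan's own figure.** Normal approximation: n = 2 × (1.960 + 0.842)² × 15² / 7.5² = 62.8, so 63 per arm. The t-based calculation gives 63.8, so 64, with power 0.801. Dropout: 64 / 0.95 = 67.4, so 68. The stated 64 and 68 per arm reproduce.

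**2. Precision.** SE = 15 × √(2/64) = 2.65. Half-width = t(0.975, 126) × SE = 1.979 × 2.652 = 5.25. A positive estimate is non-significant below 5.25, so the upper limit of a non-significant result can reach 5.25 + 5.25 = 10.5.

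**3. When the interval excludes an important difference m.** The estimate must lie below m − 5.25. The chance of this if the true effect is zero is Φ((m − 5.25)/2.652).

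| m | Estimate must be below | Chance of excluding m if true effect is 0 | Chance of non-significance if true effect is m |
|---|---|---|---|
| 7.5 | 2.25 | 80% | 20% |
| 6.3 | 1.05 | 65% | about 35% (power 0.655) |
| 5 | −0.25 | 46% | about 53% (power 0.465) |

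**4. Size of the ambiguous zone for 7.5.** Estimates from 2.25 to 5.25 are non-significant with an upper limit of at least 7.5.
- True effect 0: Φ(5.25/2.652) − Φ(2.25/2.652) = 0.976 − 0.802 = 0.174, about 17% of all trials.
- True effect 3.75: about 43%.

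**5. What an interval-based rule changes.** If 'unnecessary' requires an upper limit below 7.5, the chance of reaching that conclusion wrongly is:
- true effect 7.5: Φ((2.25 − 7.5)/2.652) = 2.4%, against 20% if every non-significant result counts;
- true effect 6.3: Φ((2.25 − 6.3)/2.652) = 6%, against about 35%.

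**6. Sensitivity.** With all 68 per arm analysed, the half-width is 5.09 and the picture is the same. If the SD were 20 (an assumption), the half-width would be 7.0, and the chance of excluding 7.5 with no true effect would fall from 80% to 56%.

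**The case against.** The strongest reply is that no decision rule exists here. Both sentences are discussion prose, they are conditional, and providing evidence is weaker than declaring. The Statistical analysis section draws no such inference and commits to 95% intervals, so a reader of the results would see the upper limit. The main Discussion also concedes that 80% power may be thought low and that a type II error is possible. An interpretation rule might sit in an analysis plan that is not shown.

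Much of this stands. It means that an inconclusive result could be reported as negative, not that it would be. But the intervals are given no role in the conclusion, and conceding a type II error sits awkwardly beside treating a null result as evidence that the block is unnecessary. The inference is stated in the article itself, so it is not merely a detail left to another document.

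A reader might go further and infer that the design cannot exclude an important benefit. The figures do not support that: with no true effect it excludes 7.5 about 80% of the time and 6.3 about 65%. An estimate of zero has an upper limit of 5.25, which excludes both, although not the lower end of the 5 to 7 range.

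A reader might also infer that 7.5 was set above everything in the literature. It was not. The article also cites 10, even though it later calls that value out of step with current literature, and it gives reasons for 7.5. The lower power at 6.3 is a sensitivity figure, not a sample size error.

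Finally, a significant estimate can be as small as about 5.25, below 7.5. Little follows from this, because the abstract claims only improvement for a significant result, not improvement beyond the MCID.

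**Conclusion.** The concern holds in a limited form. In two places the article treats failure to show superiority as evidence that the block is unnecessary, and nothing links that conclusion to the interval. At the planned precision, non-significant estimates between about 2.25 and 5.25 would remain compatible with the protocol's own MCID and should be called inconclusive. Non-significant estimates below about 2.25 would justify a negative conclusion against 7.5.

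The figures assume an SD of 15, 64 analysed per arm and an approximately normal estimate. A larger SD or fewer patients would widen the ambiguous zone. The test, the sample size and the choice of 7.5 are not faulted.

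**What to change.** Amend the abstract's Discussion paragraph and the matching sentence in the main Discussion so that they say, in substance:

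- The absence of a worthwhile benefit, or that the block is unnecessary, will be concluded only if the upper 95% confidence limit for the QoR-40 difference (block minus placebo) is below 7.5.
- Whether that limit also lies below 6.3 will be reported alongside. An upper limit of 7.0, for example, would meet the 7.5 criterion but would be shown not to exclude 6.3.
- Any other non-significant result will be described as inconclusive.

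The cost is wording only: no new data, no extra patients and no change to the primary test. The price is that some null results can no longer be called negative: about 17% of all trials if the true effect is zero. The article describes recruitment as under way, so the rule should be fixed before any results are known.

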**Trial registration:**

ClinicalTrials.gov ACTRN12619000028101. Prospectively registered on 11 January 2019 with Australia New Zealand Clinical Trials Registry

## Background

Anterior cervical discectomy and fusion (ACDF) is a common surgical procedure for cervical spine disease. There has been an increasing focus on reducing the length of hospital stay after this procedure. Whilst the mean length of stay has been reported to be approximately 2 days, some centres are performing this procedure in an outpatient setting [1–4]. The approach for anterior cervical disc arthroplasty is the same for ACDF, and there is a trend towards performing this procedure in the outpatient setting too [5]. We will hereafter refer to these two operations under the heading anterior cervical spine surgery (ACSS).

Postoperative pain and nausea are the most common reasons for prolonged hospital stay and readmission after ACSS. [6, 7] Pre-emptive analgesia with regional anaesthesia is a method used to improve postoperative pain management. The superficial cervical plexus block (SCPB) has been used for neck surgeries for this reason [8]. The cervical plexus is formed by the anterior rami of the upper four cervical nerves and lies deep to the prevertebral fascia on the scalenus medius. In a SCPB, local anaesthesia is infiltrated at the punctum nervosum, anaesthetising four superficial branches of the cervical plexus: the lesser occipital, the great auricular, the transverse cervical, and the supraclavicular nerves. The distribution of these nerves includes the anterior and lateral neck, and the pre- and post-auricular areas.

SCPB is a safe technique that has been shown to provide good relief for incisional pain after thyroid and carotid surgeries, and relief of occipitonuchal pain after neurosurgical procedures [8–11]. It may also reduce opioid consumption and therefore the related side effects, such as nausea, vomiting, and respiratory depression. Finally, a goal of the SCPB is to improve the overall quality of recovery from surgery from the patient’s perspective.

The aim of this study is to investigate the effect bilateral cervical plexus block with local anaesthesia has on postoperative recovery in patients undergoing ACSS. The hypothesis is that bilateral SCPB is superior to placebo in patients undergoing ACSS in improving post-operative recovery, as measured by the 40-item quality of recovery (QoR-40) score at 24 h.

## Methods

### Design

This is a protocol for a pragmatic, multi-centre, blinded, parallel-group, randomised controlled placebo trial. The trial is being conducted in two metropolitan academic hospitals in Sydney, Australia (Macquarie University Hospital and Nepean Public Hospital).

All patients will undergo general anaesthesia (GA). The patients randomised to the intervention group will have a SCPB administered under ultrasound guidance with a local anaesthetic solution, whilst patients randomised to the placebo group will be injected with a saline solution. All patients will be admitted to the high dependency unit (HDU) post-operatively, which is routine practice in the primary centre.

The primary endpoint is the QoR-40 score at 24 h after surgery. It will be measured by blinded assessors. A participant timeline can be found in Fig. 1.

**Fig. 1 Fig1:**
[figure not shown]
Participant timeline

The trial design is pragmatic to focus on real-world patient-orientated outcomes, rather than trying to measure efficacy in an ideal scenario. As such, the inclusion criteria are based on the type of surgery being performed rather than the indication for surgery. Also, the retractor system and interbody devices used were not pre-specified, but based on the surgeon’s preference.

The trial was prospectively registered with the Australian New Zealand Clinical Trials Registry (ACTRN12619000028101).

### Study population and recruitment

Consecutive patients who present to one of the trial neurosurgeons rooms, hospital clinic or hospital emergency department will be assessed for eligibility after they have been consented to undergo ACSS. There are no financial incentives to patients or investigators to encourage enrolment. The eligibility criteria are listed below.

Inclusion criteria:
Age ≥ 16 years oldUndergoing anterior cervical discectomy and fusionUndergoing anterior cervical disc arthroplastyIsolated cervical spine trauma requiring anterior fusion only

Exclusion criteria:
Multi-traumaUndergoing anterior cervical vertebrectomy and reconstructionUndergoing posterior fixation in addition to anterior surgeryUndergoing surgery for malignancyAllergy to ropivacaine or bupivacainePregnant patientsNeurologic or psychiatric condition that would prevent completion of the QoR-40 questionnaire

If the patient meets the eligibility criteria, they will be provided with a patient information and consent form, and be given time to read it, before undergoing an informed consent process with their treating neurosurgeon. All patients will receive a study enrolment number and baseline data will be obtained. Patients will be free to withdraw from the study at any time without giving a reason.

In addition to standard demographic information, other baseline data collected will include smoking history, pre-operative opioid use, adjuvant analgesia use, indication for ACSS and history of previous spine surgery.

### Intervention

All patients will receive standardised monitoring and one of two standardised anaesthetic regimens at the discretion of the primary anaesthetist.

Option 1: Induction with intravenous fentanyl, propofol and a non-depolarising muscle relaxant to facilitate intubation followed by maintenance with oxygen, air and sevoflurane.

Option 2: Induction using a total intravenous anaesthetic technique using Propofol and Remifentanil and infusions and a non-depolarising muscle relaxant and then maintenance with Propofol and Remifentanil infusions. This is usually indicated in patients where volatile anaesthesia may interfere with intra-operative neuromonitoring such as motor and sensory evoked potentials.

With either standardised regime, immediately after induction of anaesthesia, bilateral ultrasound-guided SCPB is placed by an anaesthetist experienced in delivering the block. Patients randomised to the local anaesthetic group will receive 15mL of 0.2% ropivacaine on each side (totaling 30mLs); the placebo group will receive 15mLs of 0.9% saline on each side. The cervical plexus is composed of purely sensory nerves, so a low concentration local anaesthetic was chosen to reduce the risk of local anaesthetic toxicity and inadvertent motor block [12].

All patients will receive skin infiltration at the incision site of 5mls of 0.25% bupivicaine with 1:400,000 adrenaline by the surgeon prior to incision, a local standard of care.

The technique for the SCPB described below is similar to the method described by the New York Society of Regional Anaesthesia for ultrasound-guided SCPB [13].

After the patient is positioned and the skin prepared with a chlorhexidine-alcohol scrub, the transducer is placed on the neck, overlying the sternocleidomastoid muscle (SCM) at its midpoint (approximately the level of the cricoid cartilage). Once the SCM is identified, the transducer is moved posteriorly until the tapering posterior edge is positioned in the middle of the screen. At this point, the brachial plexus and/or the interscalene groove (between the anterior and middle scalene muscles) should be identified. Then, the needle is passed through the skin, platysma and investing layer of fascia, placing the tip adjacent to the superficial cervical plexus. 15mL of the solution is administered to envelop the plexus.

Intraoperatively, all patients will receive 4mg of intravenous (IV) dexamethasone after induction as prophylaxis for postoperative nausea and vomiting (PONV) and may prolong the duration of the block anaesthesia and before surgical incision. Approaching closure of the wound, patients will receive 1g of IV paracetamol followed by 4mg of IV ondansetron or 1mg or IV granisetron for PONV prophylaxis.

Additional analgesia will be provided with incremental boluses of opioids at the discretion of the anaesthetist. At the end of the surgery, maintenance of anaesthesia either sevoflurane or propofol and remifentanil will be turned off and the neuromuscular blockade will be reversed with neostigmine (50 mg/kg IV) and glycopyrrolate (10 mcg/kg IV) or sugammadex.

Patients will then be taken to the post-anaesthetic care unit and then to the HDU, or directly to the HDU. The general post-operative care of the patients will be directed by the local standard practice in terms of monitoring and assessment of neurological status, pain, PONV and level of sedation.

Patients will be asked to rate their pain upon arrival and at regular intervals using an 11 point Numerical Rating Scale by the recovery nurse (0 = no pain to 10 = the worst pain imaginable; D= difficult to assess, U= unconscious). This score is recorded separately when at rest and with patient movement. The character of pain will be recorded as one of five choices (dull, pressure, radiating, sharp, throbbing). Nausea and vomiting will be assessed using a scoring system (0= no nausea 1= occasional nausea, 3= nausea and occasional vomiting, 4= constant vomiting). The level of sedation will be recorded using an analogue score (0= wide awake, 1= easy to rouse, 2= drowsy, 3= difficult to rouse, 4= unrousable). To maintain a pain score of <4, or the patient being clinically comfortable, an opioid will be administered IV every 2 to 5 min as needed. The choice of opioids will be at the discretion of the anaesthetist.

Difficulty with postoperative nausea and vomiting will be treated with 0.5mg of IV droperidol and/or 4mg of IV Ondansetron. In the first post-operative day, patients will receive regular paracetamol (1g four times a day) and oral opiates or a patient controlled analgesia (PCA), at the discretion of the anaesthetist.

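### Neostigmine reversal dose is printed in mg/kg, apparently 1,000 times too high; correct to mcg/kg once confirmed

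*Protocol article*

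**What the plan says.** The Intervention section of the protocol article sets out the anaesthetic care that every patient receives, whichever arm they are in. For the end of surgery it states that "the neuromuscular blockade will be reversed with neostigmine" and glycopyrrolate, or with sugammadex. The doses printed for the first option are "neostigmine (50 mg/kg IV) and glycopyrrolate (10 mcg/kg IV").

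The two drugs are given together by the same route, and their doses appear side by side in different units: milligrams per kilogram for neostigmine, micrograms per kilogram for glycopyrrolate. No other section of the article gives a neostigmine dose. The Trial status section identifies the text as protocol version 11, dated 11/6/21, and reports 17 patients recruited.

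**The concern.** A dose of 50 mg/kg of an intravenous reversal drug amounts to grams per patient. Its partner in the same sentence is dosed in micrograms per kilogram and amounts to about a milligram or less. The pattern is that of a unit misprint, `mg` set where `mcg` was meant.

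This is not an omission that a condensed article may leave to the full protocol. The article states a dose, and the dose as stated is implausible. The sentence is part of the care described for both arms, so any patient reversed by this route would be endangered if it were followed literally. The trial was still recruiting at publication: 136 − 17 = 119 of the planned patients were yet to be enrolled. That figure shows only that a correction was timely. It does not count patients exposed to anything.

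**Working it through.** **Inputs**

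- Neostigmine, as printed: 50 mg/kg IV (Intervention).
- Glycopyrrolate, as printed: 10 mcg/kg IV (Intervention).
- Body weight: the article gives no weights and the eligibility criteria set no weight limit. I assume 40, 70 and 120 kg to span a plausible range.

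**Dose per patient = dose per kg × weight**

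| Assumed weight | Neostigmine as printed (50 mg/kg) | Neostigmine if 50 mcg/kg | Glycopyrrolate (10 mcg/kg) |
|---|---|---|---|
| 40 kg | 50 × 40 = 2,000 mg = 2.0 g | 2.0 mg | 0.4 mg |
| 70 kg | 50 × 70 = 3,500 mg = 3.5 g | 3.5 mg | 0.7 mg |
| 120 kg | 50 × 120 = 6,000 mg = 6.0 g | 6.0 mg | 1.2 mg |

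**Mass ratio, neostigmine to glycopyrrolate**

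- As printed: 2,000/0.4 = 3,500/0.7 = 6,000/1.2 = 5,000.
- With mcg/kg: 2.0/0.4 = 3.5/0.7 = 6.0/1.2 = 5.

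Weight cancels, so each ratio holds for any patient. The two readings differ by 5,000/5 = 1,000.

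**Comparison with the other fixed IV doses in the same section**

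These are droperidol 0.5 mg, granisetron 1 mg, ondansetron 4 mg, dexamethasone 4 mg and paracetamol 1 g. At 70 kg the printed neostigmine dose would be 3.5 times the largest of them. With mcg/kg it would be 3.5 mg, among the milligram doses.

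**Does it touch the trial's statistics?**

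No. The sample size uses only the target difference ("We used an MCID of 7.5 for the QoR-40, as discussed above"), the standard deviation of 15 given under Primary outcome ("undergoing spinal surgery was 160 (SD-15")), power 0.8 and two-sided alpha 0.05:

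- Normal approximation: n = 2 × (1.960 + 0.842)² × (15/7.5)² = 2 × 7.85 × 4 = 62.8, so 63 per group.
- With the t distribution: 63.8, so 64 per group, which is the plan's figure.
- Dropout of 5%: 64/0.95 = 67.4, so 68 per group and 136 in total, again as planned.

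No drug dose enters this calculation or the analysis of the primary outcome.

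**The case against.** Five points can be made on the other side.

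1. **The article does not prove the error by itself.** It gives no reference dose for neostigmine, and two drugs in one sentence need not share a unit or have similar masses. The same section gives 1 g of paracetamol alongside 1 mg of granisetron and 0.5 mg of droperidol, ratios of 1,000:1 and 2,000:1. This is fair as far as it goes: the 5,000:1 ratio alone is not proof, and the corrected unit is an inference from the paired drug and from general dosing plausibility. What stands is the need to confirm the unit before changing it. Even this case accepts that a misprint is the likely reading.

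2. **The slip may exist only in the article,** introduced in typesetting or text extraction. That cannot be excluded without the original page. It is less likely than it first seems, because the same sentence spells the smaller unit in Latin letters ("glycopyrrolate (10 mcg/kg IV) or sugammadex"). A lost Greek mu would require two notations for one unit within a sentence.

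3. **Harm in practice is unlikely.** Neostigmine is not a study drug, sugammadex is offered as an alternative, and an experienced anaesthetist would very probably notice. Nothing shows that sites dose from this article. All of this stands, and it is why the point says nothing about what patients actually received.

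4. **There is no effect on inference.** This is correct and rules out a higher grade. It does not make a 1,000-fold error in a stated weight-based intravenous dose cosmetic.

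5. **The 119 patients still to be recruited suggest an exposure that is not shown.** The subtraction is right, but the number is context only.

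**Conclusion.** The concern holds. As printed, the neostigmine dose is 2.0 to 6.0 g at assumed weights of 40 to 120 kg, against 2.0 to 6.0 mg if the unit is mcg/kg. That is a factor of 1,000 at any weight.

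Confidence is high that the text prints mg/kg and that this cannot be the intended dose. That 50 mcg/kg is the right replacement is a strong inference, but the article cannot settle it. Nor can it show whether the approved protocol or any site document carries the same unit.

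This is a text error with a safety aspect, in background care common to both arms. It should be fixed. It has no bearing on the randomised comparison, the sample size or the analysis.

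**What to change.** Confirm the intended dose against the approved protocol and a pharmacy reference. Once confirmed, change the neostigmine unit from `mg/kg` to `mcg/kg`, so that the sentence gives neostigmine 50 mcg/kg IV with glycopyrrolate 10 mcg/kg IV, and correct the published article accordingly. Check that the full protocol, the version on the trial registry and any site anaesthetic instructions do not carry the printed unit.

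The cost is one unit in one sentence plus a document check. Design, sample size and analysis stay as they are.
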